### Potential mechanisms of change

To determine whether TRE specifically shifts sleep and day/night rhythms (hypothesized mechanisms), we will examine changes in sleep (the gold standard CORE CSD measures of quality of sleep and reduced variability in sleep midpoint, along with PROMIS sleep disturbance and sleep-related impairment) and day/night rhythms (BSRS and the MCTQ). To assess whether the sleep and light guidance offered as part of the TRE intervention leads to improved sleep hygiene, we will gather the Sleep Household Environment and In-Bed Behaviors [98].

### Potential moderators

We chose to include participants taking a broad range of medications to enhance the generalizability of the sample. To examine how medication levels shape intervention effects on circadian and symptom outcomes, we will gather the types of psychotropic and sleep medicines, doses, and adherence levels at each self-report assessment to calculate summary scores for each receptor type. At baseline, we will gather data on self-rated personality symptoms using the Personality Inventory for DSM-5, the Brief Form Plus (PID5BF + ; [102]), the Positive Urgency Scale [143], food insecurity (HFSSM; [100, 144]), Menopause QoL sleep items [104, 105], and early adversity (the Risky Families Scale; [145]) as potential predictors of intervention outcome.

## Reasons for discontinuation from study

Participants requesting to withdraw from the study will be asked to complete an intervention acceptability survey and final assessment of symptoms (self-rated mania, depression, and QoL; and, if willing, the YMRS, MADRS, and the LIFE. They will be asked (via a brief phone call from a trial coordinator) the main reasons for discontinuation. Should adverse events be discovered, those will be reported.

## Statistical analysis plan

We chose our sample size to support showing a moderate effect size for changes in symptoms in the TRE vs. control conditions (f2 = 0.25). We planned for 33% attrition based on previous online intervention studies in BD, to support a sample size of 200. A sample size of 200 provides > 80% power (1-*β*) to detect an effect of this size at α = 0.05 (two-tailed) and to detect changes in TRE compared to those of the Mediterranean diet within those with early onset (estimated to be one-third of the sample).

Before conducting the analyses, we will examine whether the assumptions for missing value imputation are met (e.g., whether values appear to be missing at random). If those assumptions are supported, we will impute data using 20 resamples, using demographic (gender, age), baseline symptom severity, and symptom history variables (number of episodes) to predict missing scores. For comparison, we will perform analyses without imputed values.

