**Methods:**

This study is an international RCT to compare the effectiveness of TRE and the Mediterranean diet. Three hundred participants will be recruited primarily via social media. Main inclusion criteria are: receiving treatment for a diagnosis of BD I or II (confirmed via DIAMOND structured diagnostic interview), endorsement of sleep or circadian problems, self-reported eating window of ≥ 12 h, and no current mood episode, acute suicidality, eating disorder, psychosis, alcohol or substance use disorder, or other health conditions that would interfere with or limit the safety of following the dietary guidance. Participants will be asked to complete baseline daily food logging for two weeks and then will be randomly allocated to follow TRE or the Mediterranean diet for 8 weeks, during which time, they will continue to complete daily food logging. Intervention content will be delivered via an app. Symptom severity interviews will be conducted at baseline; mid-intervention (4 weeks after the intervention begins); end of intervention; and at 6, 9, and 15 months post-baseline by phone or videoconference. Self-rated symptom severity and quality of life data will be gathered at those timepoints, as well as at 16 weeks post baseline. To provide a more refined index of whether TRE successfully decreases emotional lability and improves sleep, participants will be asked to complete a sleep diary (core CSD) each morning and complete six mood assessments per day for eight days at baseline and again at mid-intervention.

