### Hypotheses

This is a hybrid trial designed to assess acceptability and efficacy.H1: Compared with the control intervention, TRE will lead to improvements in interview-based mania and depression scores immediately postintervention, which will manifest in downstream improvements in self-rated quality of life (QoL) at 6 months compared to baseline.H2: To extend findings to BD, in that TRE will be rated as highly acceptable, and patients will exhibit high adherence.H3: Compared with those of a control intervention, the effects of TRE will be more powerful earlier in the course of the disorder (< 5 years from onset) than later in the course of the disorder.H4: Compared with those of a control intervention, the effects of TRE on symptoms will be more sustained at 6, 9, and 15 months. The effects of TRE on QoL, compared to those of a control intervention, will be sustained for 6, 9, and 15 months.H5: Compared with a control intervention, TRE will lead to improvements in self-rated symptoms of mania and depression at the end of intervention and at 3.5, 6, 9, and 15 months after baseline compared to baseline symptom severity scores.

We will conduct intent-to-treat analyses but will conduct sensitivity analyses to consider effects among those who adhere to interventions.

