## Trial design

The trial is a prospective, rater-blind, superiority randomized controlled trial (RCT) with a one-to-one allocation ratio comparing TRE with the Mediterranean diet. Participants in both conditions will be asked to sustain ongoing medical care for BD.

The primary endpoint is immediately postintervention (at completion of the 8-week intervention). The follow-up times are 6, 9, and 15 months after the baseline, with an additional 16 weeks post-baseline self-reported assessment. The study setting is remote (online).

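### The sizing statement calls f2 = 0.25 moderate, but for two equal arms it is a 1.0 SD difference; if 0.5 SD was meant, power in the early-illness third is about 52%, not above 80%

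*Protocol article*

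**What the plan says.** The Statistical analysis plan section gives the target as "a moderate effect size for changes in symptoms in the TRE vs. control conditions (f2 = 0.25". On attrition it says: "We planned for 33% attrition based on previous online intervention studies in BD, to support a sample size of 200". The abstract gives the matching recruitment figure: "Three hundred participants will be recruited". The power sentence begins "A sample size of 200 provides > 80% power" and sets the test "at α = 0.05 (two-tailed". The same sentence extends the power claim to detecting changes under TRE compared with the Mediterranean diet "within those with early onset (estimated to be one-third of the sample".

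Trial design describes a "superiority randomized controlled trial (RCT) with a one-to-one allocation ratio comparing TRE with the Mediterranean diet". Under Hypotheses, H3 says that, compared with a control intervention, "the effects of TRE will be more powerful earlier in the course of the disorder" (less than 5 years from onset) than later.

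The article gives no SD, no difference in scale points, no baseline correlation and no separate effect size for the subgroup.

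**The concern.** The label and the number describe effects of quite different size. In a comparison of two equal arms, f2 = 0.25 is a full standard deviation, whereas moderate is normally read as about half of one. Because the power claim rests on this one input, a reader cannot tell which effect the trial is sized for.

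For the overall comparison this hardly matters, since 200 participants are enough under either reading. It matters for the early-illness subgroup, which recruitment deliberately oversamples (Inclusion/Exclusion criteria). Someone who takes the word moderate at face value would treat a null result in about 67 people as well powered, although at 0.5 SD it would be close to a coin toss.

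There is a second gap. H3 compares early with late illness, which is an arm-by-stage interaction. The only subgroup power quoted is for TRE against the Mediterranean diet inside the early group, which is a different and easier question.

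**Working it through.** **Inputs from the protocol article.** f2 = 0.25, two-sided alpha 0.05, 200 analysable participants, 33% attrition from 300, one third in the early subgroup (all Statistical analysis plan, with 300 from the abstract), and 1:1 allocation (Trial design). One third of 200 is about 67, or 33 and 34 per arm, leaving 133 with later illness.

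**Attrition.** 300 × (1 − 0.33) = 201 and 300 × 2/3 = 200. The stated 200 is reproduced.

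**Converting the effect size.** For two equal arms d = 2f, so d = 2 × √f2.
- f2 = 0.25: f = 0.5, d = 1.0 SD.
- f = 0.25: f2 = 0.0625, d = 0.5 SD.
- f2 = 0.15: d = 2 × √0.15 = 0.77 SD.

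**Power.** Two-sample t-test on the analysed outcome, noncentral t with noncentrality d × √(n1·n2/(n1 + n2)).

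| Effect | n = 200 | n = 67 | Total for 80% |
|---|---|---|---|
| 1.0 SD (f2 = 0.25 as printed) | > 99.9% | 98% | 34 |
| 0.77 SD (f2 = 0.15) | > 99.9% | 88% | – |
| 0.5 SD (f = 0.25) | 94% | 52% | 128 |

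The claim of more than 80% is therefore reproduced, as an inequality, at the printed f2, both overall and in the subgroup. At 0.5 SD it is reproduced overall but not in the subgroup.

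**Would baseline adjustment rescue the subgroup at 0.5 SD?** Suppose 0.5 SD is on the raw-score SD and the analysis adjusts for baseline with correlation r. The effective difference is then 0.5/√(1 − r²). The article gives no r, so these values are assumptions:
- r = 0.3: 0.524, power 56%
- r = 0.5: 0.577, power 64%
- r = 0.6: 0.625, power 71%
- r = 0.7: 0.700, power 81%

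**Difference detectable with 80% power at n = 67.** About 0.69 SD unadjusted. With r = 0.5 it is 0.69 × √0.75 = 0.60 SD.

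**If one third of all 300 were meant (n = 100, no attrition).** Power at 0.5 SD is 70%, still below 80%.

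**H3 as an interaction (67 early, 133 late, 1:1 within each).** SE of the difference between the two treatment effects = √(4/67 + 4/133) = 0.300 SD. Normal approximation:
- effects differ by 0.5 SD: Φ(0.5/0.300 − 1.96) = 39%
- effects differ by 0.25 SD: 13%
- 80% power needs (1.96 + 0.84) × 0.300 = 0.84 SD

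**The case against.** Three stronger readings are tempting, and the document supports none of them.

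*The stated power is false.* It is not. At the printed f2 = 0.25 both claims hold comfortably. On the usual f2 benchmarks (0.15 medium, 0.35 large) the value lies between medium and large, so the label has some defence on that scale. Even f2 = 0.15 gives 88% in the subgroup. This stands. What remains is that f2 = 0.15 is already 0.77 SD in a two-arm comparison, well above what most readers would take moderate to mean.

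*The authors plainly wrote f2 for f.* This is plausible, because f = 0.25 fits both the word moderate and a target of 200, but it is an inference. A within-between repeated-measures calculation with f = 0.25 and an assumed correlation of 0.5 gives 98% at n = 67, so an f of 0.25 and high subgroup power can come from one calculation. That setting again implies a 1.0 SD difference in change, so it does not rescue 0.5 SD. It does mean that an f of 0.25 need not stand for 0.5 SD. Also, the early-onset clause names no effect size of its own, and H3 expects a larger effect early; an effect of 0.69 SD would suffice.

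*H3 will be declared confirmed from a p-value inside the early subgroup.* Nothing in the article says so. The test for H3 is not described there and may be in an analysis plan that is not shown. Its absence is no fault. The limited point is that the power quoted is not power for H3.

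**Conclusion.** The label moderate, the printed f2 = 0.25 and more than 80% power in the early third do not hold together if moderate means 0.5 SD. As printed, the trial is sized on a 1.0 SD difference between two active diets. The power claim is then true, but 34 participants would be enough and the target of 200 is unexplained. Under the 0.5 SD reading the target makes sense and overall power is 94%, but subgroup power is about 52% (56% to 81% at assumed baseline correlations of 0.3 to 0.7).

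On either reading the quoted subgroup power does not speak to H3, whose interaction has about 39% power for a 0.5 SD difference in effects.

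These figures assume 200 completers, one third with early illness, equal arms, and a single between-arm comparison of the analysed outcome. The overall comparison keeps at least 94% power for any effect of 0.5 SD or more. This is therefore a correction to a stated sizing figure and does not threaten the main result.

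**What to change.** State the target difference in SD units or scale points, on a named outcome, and make the label and the number agree. The authors know which value they used and should choose between:

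- **If 0.5 SD was meant:** give f = 0.25 (0.5 SD) with 94% power at 200. Replace the subgroup claim with about 52% to 64% power at 0.5 SD (no adjustment, and baseline correlation 0.5), with 80% reached only for about 0.60 to 0.69 SD.
- **If f2 = 0.25 was meant:** keep it, state that it is a 1.0 SD difference between arms, and delete moderate.

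In both cases add one sentence saying that the subgroup power refers to TRE against the Mediterranean diet within early illness and does not cover the early-versus-late comparison in H3. That comparison has about 39% power if the effects differ by 0.5 SD, and reaches 80% only for a difference of about 0.84 SD.

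The cost is a few lines of text and, on the first option, a less favourable subgroup figure. No extra participants are needed, and the design and primary analysis do not change.

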### Data cleaning

In addition to reviewing careless responses during screening, we will review each self-report bundle for careless responding. We will qualitatively review and consider excluding questionnaire bundles where a person has responded with the same response more than 14 times in a row or has a high Mahalanobis distance score.

### Statistical analysis of the primary outcome

Changes in mania, depression, and QoL from baseline to immediately postintervention are hypothesized to be significantly greater in the TRE intervention than in the Mediterranean diet intervention. We will test this using a multivariate repeated measures linear mixed model analysis with random effects. All intervention-related effects will be estimated using an intention-to-treat approach, in which we will examine final scores (where available) for all randomized participants. To support intent-to-treat analyses, we will attempt to gather final assessments for all participants who discontinue the study (except those who explicitly discontinued or were withdrawn on ethical grounds). For H2, we will provide descriptive information, and we will test the hypothesis that relative to the Mediterranean Diet, the TRE condition will be associated with decreased attrition and higher ratings of satisfaction with the intervention. Statistical analyses will be conducted in accordance with the International Conference on Harmonization E9 statistical principles.

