## Strategies to maximize data quality

As noted above, we will exclude participants who provided careless responses during the screening questionnaire. In self-rated assessments during the intervention and follow-up, we will exclude data from any bundle in which participants fail 50% or more of the attention checks [1] or when the mean duration for completion of standard multiple-choice questions is < 2 s. At the midpoint, at the end of the intervention, and at the follow-up assessments, we will ask participants whether we should exclude their data from that session due to problems with attention or understanding. Comprehensive data cleaning (range and other distributional checks, comparison with published norms where relevant) will be conducted before the analyses.

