All sources of information will be monitored in a timely manner to consider potential adverse events. Where clinical deterioration is noted as potentially emerging, researchers will attempt to assess whether emergent symptoms or concerns appear in any way connected to the intervention or study procedures. If EDE-QS symptoms are above the clinical threshold after enrollment, we will include a probe to assess intervention effects on those symptoms (e.g., do you believe that this intervention has triggered food or appearance symptoms for you?), and we will conduct clinical interviews to consider deterioration of symptoms. Participants will be withdrawn from the trial if their participation compromises clinical care as determined by the study’s executive committee. On a case-by-case basis, this might include instances of hospital admission, acute hypomania or mania, psychotic symptoms, active suicidal intent, or increased eating disorder symptoms, particularly where there is concern that deterioration is related to trial engagement.

Adverse events will be reviewed at monthly executive meetings and at least annual meetings of the independent trial committee (who will consider patterns of adverse events by condition). Adverse events will be promptly reported to the Committee for the Protection of Human Subjects within one week.

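### Final scores are not sought from participants withdrawn on ethical grounds, so primary outcomes may be missing because of the outcome itself

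*Protocol article*

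**What the plan says.** In the protocol article, the section Statistical analysis of the primary outcome describes an intention-to-treat approach "in which we will examine final scores (where available) for all randomized participants". To support it, the team will try to obtain final assessments from everyone who discontinues, "except those who explicitly discontinued or were withdrawn on ethical grounds".

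The article does not define ethical grounds. The only text on withdrawal by the study team is under Adverse events: "Participants will be withdrawn from the trial if their participation compromises clinical care", as judged by the executive committee. Case by case, "this might include instances of hospital admission, acute hypomania or mania, psychotic symptoms, active suicidal intent, or increased eating disorder symptoms", and "particularly where there is concern that deterioration is related to trial engagement".

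Reasons for discontinuation from study deals with people who leave at their own request: "Participants requesting to withdraw from the study will be asked to complete an intervention acceptability survey and final assessment of symptoms". That assessment covers self-rated mania, depression and quality of life and, if the person is willing, the YMRS, MADRS and LIFE.

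The opening of the Statistical analysis plan section imputes missing scores if they appear to be missing at random, using gender, age, baseline symptom severity and number of episodes, and adds an analysis without imputation. The section Sensitivity analysis of the primary outcome keeps only participants with baseline and post-intervention symptom assessments and at least 80% adherence.

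**The concern.** The primary measures are the MADRS, YMRS and LIFE, and quality of life is in the primary model. Several of the events that may lead to withdrawal by the team are severe forms of what these scales measure. A rule that does not seek final scores after such a withdrawal can make the outcome missing because it was bad. Withdrawal is also more likely where the deterioration is suspected to come from taking part, so the loss may depend on the assigned arm.

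If one arm loses more such scores than the other, that arm looks better than it was. This could favour either diet. A missing-at-random analysis does not remove the problem when the reason for the missing score is not among its predictors.

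There is also a conflict of wording. One section exempts those who explicitly discontinued from the attempt to gather a final assessment, while another says that people who request withdrawal will be asked for one. As written, staff cannot follow both.

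**Working it through.** **The plan's own figure.** Stated inputs are 300 recruited, 33% attrition and 200 evaluable, with more than 80% power at two-sided 0.05. Inflation gives 200 / (1 − 0.33) = 298.5, so 299 against 300 stated; this reproduces. With 100 per arm, power is 0.94 if 0.25 is read as Cohen's f (d = 0.5), and above 0.999 if it is read literally as f² (d = 1.0). The standardised difference detectable with 80% power is (1.96 + 0.84) × √(2/100) = 0.40 SD. The point does not depend on these figures; they give a scale for the results below.

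**Do other sections bring the lost scores back?**
- The exit assessment in Reasons for discontinuation from study is for people who ask to leave. It does not cover people whom the team withdraws.
- The imputation predictors are all baseline or history variables. None carries deterioration after randomization or the reason for withdrawal. Observed data cannot establish that scores are missing at random.
- The sensitivity analysis requires a post-intervention assessment and high adherence, so it leaves the same people out.

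**Size.** The documents give neither withdrawal rates nor severity, so both are assumed. Let pT and pC be the shares withdrawn for deterioration in the TRE and Mediterranean diet arms, and let m be how many SD worse they end than the others in their arm. Each full arm mean is the mean of those who stay plus p × m, while the observed mean omits that term. The hidden difference is therefore m × (pT − pC), or pT × mT − pC × mC if severity differs by arm.

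| Withdrawn, TRE v Mediterranean diet | m = 1 | m = 1.5 | m = 2 |
|---|---|---|---|
| 2% v 2%, or 5% v 5% | 0 | 0 | 0 |
| 5% v 2% | 0.03 | 0.045 | 0.06 |
| 10% v 5% | 0.05 | 0.075 | 0.10 |
| 10% v 2% | 0.08 | 0.12 | 0.16 |

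Entries are in SD units. For example, 2 × (0.10 − 0.02) = 0.16, which is 0.16 / 0.5 = 32% of d = 0.5. Swapping the arms reverses the sign.

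**Would the planned analyses recover it?** A large simulation (400,000 per arm) had no difference between arms other than the deterioration of those withdrawn, and all their final scores were missing. Results are TRE minus Mediterranean diet in SD, where higher is worse.

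| Assumed | Full data | Observed cases | Imputed from baseline | Imputed from baseline and midpoint |
|---|---|---|---|---|
| 10% v 5%, m = 1.5, half visible at midpoint | 0.077 | 0.00 | 0.00 | 0.017 |
| 10% v 5%, m = 1.5, nothing visible at midpoint | 0.073 | 0.00 | 0.00 | 0.00 |
| 10% v 2%, m = 2, half visible at midpoint | 0.161 | 0.00 | 0.00 | 0.03 |
| 5% v 5%, m = 1.5, half visible at midpoint | 0.00 | 0.00 | 0.00 | 0.00 |

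Observed cases and baseline imputation miss the difference entirely. A midpoint score that already shows half the deterioration recovers about a fifth (0.017 / 0.077 = 22%; 0.03 / 0.161 = 19%).

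**The case against.** The strongest reply is that the affected group may be small. Withdrawal is case by case, and the Adverse events section also keeps deteriorating people in the trial: it offers a break from the food plan with a later check-in, and directs participants to their own provider. A reader might infer that everyone who becomes manic, suicidal or hospitalised is withdrawn; the text says only that withdrawal might include such cases. Equating ethical grounds with these withdrawals is itself an inference, though the article describes no other withdrawal by the team.

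A reader might also say that the analysis is not intention-to-treat. That goes too far. Withdrawn people keep their baseline and any midpoint scores in the mixed model; what is lost is the final score, not the person. Nor would an excess of harm be wholly hidden, since the independent committee reviews adverse-event patterns by condition. That review does not correct the efficacy estimate, however.

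The phrase about explicit discontinuation could mean only people who refuse all further contact, which would remove the conflict with the discontinuation section. The article does not say so.

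Three further inferences are unsupported:
- Nothing indicates a gap as large as 3 or 4 SD between withdrawn participants and the rest, so much larger biases cannot be claimed.
- No text says that exit assessments will be entered as week-8 values.
- The self-report cleaning rules are a separate and weaker matter. The attention-check rule is pre-specified, and a high Mahalanobis distance only prompts a review. Among the outcomes in the primary model they touch quality of life, not the interview measures.

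**Conclusion.** The point holds in a limited form and should be fixed. The stated exception means that final primary-outcome scores may go uncollected because of the outcome, and possibly because of the arm. Neither the planned imputation nor the planned sensitivity analysis corrects this. The conflict between the analysis and discontinuation sections is on the face of the text.

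The likely size is modest against the 0.40 SD detectable difference: 0.03 to 0.16 SD over the unequal shares tried. This rests on assumed withdrawal shares of 2% to 10%, assumed severity of 1 to 2 SD, and final scores missing for all those withdrawn. With equal shares and severity the between-arm bias is about zero, although both arm means look too good. Only withdrawals within the 8 weeks affect the primary endpoint. The documents do not support a claim that the trial result will be seriously biased; they do support the claim that a modest harm confined to withdrawn participants could go unseen in the efficacy comparison.

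**What to change.** Leave the withdrawal decisions as they are, and change only what happens to follow-up afterwards.

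1. State that stopping the intervention and stopping follow-up are separate events, recorded separately with the reason.
2. Delete the exception in Statistical analysis of the primary outcome, and reconcile that section with Reasons for discontinuation from study.
3. Seek the scheduled post-intervention MADRS, YMRS, LIFE and quality-of-life assessment from every randomized participant, unless consent to follow-up is withdrawn or contact is judged clinically inappropriate for that individual. An individual, recorded judgement is narrower than exempting a whole undefined category.
4. Add a missing-not-at-random sensitivity analysis for participants withdrawn for deterioration whose final scores remain missing, for example over a range of worse assumed scores that may differ by arm.

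The cost is protocol wording, a few interviews that were already scheduled, and one extra analysis. The change needs to be made while participants are still in follow-up, because a missed post-intervention score cannot be collected later.
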